#### Engagement with the intervention (patterns of website use)

We will record website usage in order to assess engagement with the intervention (and whether this appears to be related to outcomes). The software used will record the number of times each user visits the site, the pages visited and the time spent on each topic section.

#### Adverse effects

We will record any adverse impacts on sexual health outcomes at 3, 6 and 12 months. Participants will be asked to report whether they have experienced any adverse impacts as a result of the study, recording this in a free text box on each of the follow-up questionnaires. Adverse impacts may also be identified when the research team liaise directly with participants (eg, participant emails or follow-up telephone calls to non-responders to questionnaires).

#### Intervention development costs and trial feasibility indicators

Intervention development costs and recruitment and retention rates will be reported.

### Methods to protect against sources of bias

Participants will use the tablet computer without assistance, providing baseline data that will be submitted directly online. A study researcher will be available in the clinic and via telephone, solely to clarify research procedures and assist with technical problems. Baseline data will be collected prior to randomisation. Once eligibility for the study is established and baseline data are collected, allocation to the intervention or control group will be automatically randomly assigned by computer algorithm, and this will not be changeable by participants or researchers. Subsequent outcome data will be collected online using an emailed link to the online outcome questionnaire. Data will be exported and analysed using ID numbers only. Participants will be aware of their allocation to the intervention or control group, but the automated data collection procedures protect from researcher bias during data collection.

### Maximising retention

We will follow up participants by email, texts and by telephone:^32^
^33^
Automated emails, with three further follow-up emails at weekly intervals;Two text messages—at the same time as the last two emails;Contact via telephone a week after the final email.

We will offer participants a £10 online shopping voucher for filling in the online questionnaires at 3 and 6 months, with a £20 voucher for the final 12-month follow-up questionnaire. Vouchers will be sent by email.

## Statistical analysis plan

### Sample size and power calculations

This is a pilot RCT with a primary aim of assessing the success of recruitment and retention, engagement with the intervention, and the acceptability of trial procedures to participants and clinic staff. We will also calculate the effect sizes of key outcomes including condom use over the past 3 months, to inform power calculations for a future phase III RCT.

The study is powered to allow estimates of the effect of the intervention on episodes of unprotected vaginal sex over the past 3 months. A sample size of 166 participants (83 intervention, 83 comparator, randomised 1:1 between experimental and control conditions) is adequate to detect a reduction of 1.35 episodes of unprotected sex with a conventional two-sided α of 0.05 and 90% power (1−β). Allowing for potential loss to follow-up at 3 months, a sample size of 122 participants (61 intervention, 61 comparator) is adequate to find a reduction of 1.35 episodes of unprotected sex with a conventional two-sided α of 0.05 and 80% power (1−β). In addition, this sample size is also sufficient to detect a 1.65 difference in safer sex intention, and a one-point difference in self-efficacy on Likert scales, with a conventional two-sided α of 0.05 and 90% power (1−β).

### Data analysis

#### Analysis of outcomes

Analysis of sexual health outcomes will be based on all participants according to their initial experimental allocation (on an intention-to-treat analysis). Analysis for the primary outcome will use a generalised mixed model, with log link and Poisson/mixed error. The response variable will be the number of episodes of unprotected vaginal sex for each subject. Explanatory variables will be the baseline (log_e_(x)) number of episodes of unprotected vaginal sex and the experimental condition. The analysis will include a generalised (random effects) over-dispersion parameter. Comparisons of sexual health between intervention and control groups will include the baseline value of each outcome as subject level explanatory variables, so that analysis is of the difference in end point conditional on the within-subject baseline measure. For sexual health outcomes measured only at follow-up, we will compare effect sizes between intervention and control groups alone using all available data and describe loss to follow-up for each treatment condition. For other outcomes, analyses will be based on generalised linear models with appropriate link functions and error structures. Statistical analyses will be described a priori in a Statistical Analysis Plan, and the principal analyses will be implemented independently by two statisticians.

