### Inclusion and exclusion criteria

#### Inclusion criteria

Men aged 16 years and above (with no upper age limit); able to read English; with access to the internet; and at high risk of future STI (ie, two or more partners in the past year (male or female) and some non-condom use in the past 3 months; or symptoms of acute STI; or seeking treatment for an STI); and for whom at least half of their sexual partners are female.

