#### Measures

In the light of evidence that measurement alone may prompt behaviour change,^22^ we will measure a limited number of outcomes (condom use and the main mediators, and self-reported STI diagnoses) at baseline; we will also assess a full range of outcomes at 3, 6 and 12 months (table 1). All assessments have a recall period of the previous 3 months, which is the time between follow-up assessments.

**Table 1 BMJOPEN2014007552TB1:** Variables assessed at each time point

Baseline measures	3-month, 6-month and 12-month follow-up assessments
Demographic details (age, occupation, ethnicity)	

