##### Condom use

The objective of the study is to promote condom use with female partners, so the primary outcome is the number of episodes of unprotected vaginal sex (without a condom) over the previous 3 months, assessed at the 3-month follow-up. We expect the majority of change in behaviour to occur shortly after recruitment, as we expect users will be most likely to engage with the intervention during the clinic visit.

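### The primary model adjusts for the natural log of the baseline count, which is undefined at zero, although men with a zero baseline count are eligible

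*Protocol article*

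**What the plan says.** All references are to the protocol article.

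- **Analysis of outcomes, model:** "Analysis for the primary outcome will use a generalised mixed model, with log link and Poisson/mixed error". The covariates are then named: "Explanatory variables will be the baseline (log_e_(x)) number of episodes of unprotected vaginal sex and the experimental condition". A random-effects over-dispersion parameter is added. No constant is added to the count, and no rule is given for a count of zero.
- **Analysis of outcomes, analysis set:** "Analysis of sexual health outcomes will be based on all participants according to their initial experimental allocation (on an intention-to-treat analysis".
- **Condom use:** "the primary outcome is the number of episodes of unprotected vaginal sex (without a condom) over the previous 3 months". Only vaginal episodes count.
- **Measures:** "All assessments have a recall period of the previous 3 months". The baseline count therefore also covers 3 months.
- **Inclusion criteria:** high risk of future STI can be met by behaviour, "two or more partners in the past year (male or female) and some non-condom use in the past 3 months", and also by two other routes joined to it by *or*: "or symptoms of acute STI; or seeking treatment for an STI". At least half of a man's partners must be female.

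**The concern.** The covariate and the eligibility rule do not fit together. The log of the baseline count exists only for men with at least one unprotected vaginal episode in the 3 months before enrolment, and the inclusion criteria do not require one. A randomised man with a zero count makes the fit fail or is dropped from it, although he may have reported his 3-month outcome in full. This is not loss to follow-up: his data exist and the formula rejects them.

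Three things are at stake:

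- The analysis would not cover all participants as allocated, contrary to the statement in the same section.
- Precision would be lost in a trial whose section on sample size already allows for 166 men falling to 122.
- The effect would be estimated only in men with at least one unprotected vaginal episode at baseline. The same section says that effect sizes will inform power calculations for the phase III trial, whose eligible population may well be wider.

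The principal analyses are also to be implemented independently by two statisticians. Without a stated rule, each could handle zeros differently, and the choice would be made after the data are in.

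**Working it through.** **1. Can an eligible man have x = 0?**

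| Route in Inclusion criteria | Requires a condomless vaginal episode in the past 3 months? |
|---|---|
| Symptoms of acute STI | No |
| Seeking treatment for an STI | No |
| Two or more partners in the past year and some non-condom use in the past 3 months | Not strictly: partners may be male or female and the type of act is not restricted |

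The first two routes are the main ones. The third adds less, because at least half of partners must be female.

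**2. What does the stated covariate do at x = 0?** log_e(0) is minus infinity, so the linear predictor is undefined. As a check, a Poisson regression was fitted to simulated data for 122 men, 26 of them with x = 0. With log_e(x) it stopped with a numerical error. With log_e(x+1) it used all 122. The simulation shows only the mechanism; its 26 zeros say nothing about this trial.

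**3. The plan's own sample size.** Inputs from Sample size and power calculations: difference d = 1.35 episodes; two-sided α = 0.05; 83 per arm for 90% power; 61 per arm for 80% power after loss to follow-up. No standard deviation (SD) is given, so it is back-solved:

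SD = d / [√(2/n) × (z₀.₉₇₅ + z_power)]

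- n = 83, 90%: 1.35 / [√(2/83) × (1.960 + 1.282)] = 2.68
- n = 61, 80%: 1.35 / [√(2/61) × (1.960 + 0.842)] = 2.66

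A single SD of 2.67 serves both. It gives power of 90.3% at 83 per arm and 79.7% at 61 per arm by the normal approximation (about 90% and 79% by the t distribution). The two stated sizes agree with each other.

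**4. Illustrative loss.** The share q with x = 0 is not in the documents, so it is varied from 5% to 30%. The number per arm becomes 61 × (1 − q). Normal-approximation power is Φ(d / [SD × √(2/n)] − 1.960). For q = 10%: n = 54.9 and 1.35 / [2.67 × √(2/54.9)] = 2.649, so power is Φ(0.689) = 75.5%.

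| q (assumed) | Dropped of 166 | Dropped of 122 | n per arm | Power, normal | Power, t |
|---|---|---|---|---|---|
| 0% | 0 | 0 | 61 | 79.7% | 79% |
| 5% | 8 | 6 | 58.0 | 77.7% | 77% |
| 10% | 17 | 12 | 54.9 | 75.5% | 75% |
| 20% | 33 | 24 | 48.8 | 70.5% | 70% |
| 30% | 50 | 37 | 42.7 | 64.7% | 64% |

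With a covariate defined at zero, all 122 stay in.

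**The case against.** **The notation may be shorthand.** The log stands in parentheses and may only label the scale of the covariate. The article condenses a fuller protocol and refers to a separate SAP, not shown, which may add a constant. This stands as a limit: one cannot say that the trial's analysis will exclude these men. It does not remove the point, because the article states a specific transform, and that transform fails on data its own eligibility rule allows.

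**This is a pilot.** Its stated primary aim is recruitment, retention, engagement and acceptability, so no confirmatory conclusion rests on the covariate. That stands and lowers the severity. It does not remove the point either, since the same section claims power for this outcome and carries its effect size forward.

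**The size is weakly anchored.** This stands. Nothing in the documents supports any particular share of zeros. The power figures come from an unadjusted comparison of two means, whereas the planned model is an over-dispersed Poisson model adjusted for baseline. Men with zero baselines may also have a different outcome distribution. At shares of 5% to 10% the loss is only about 2 to 4 percentage points.

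**Stronger readings that a reader might infer.** One is that dropping these men biases the comparison between arms. The documents do not support that: baseline data are submitted before allocation, so the exclusion rests on a pre-randomisation variable and the remaining men are still compared as randomised. Another is that the same fault runs through all baseline-adjusted count outcomes. The log transform is stated only for the primary outcome; for the others the text refers simply to the baseline value and to appropriate link functions.

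**Conclusion.** The point holds as an error in the wording of the primary model. The covariate is undefined at a value that eligible, randomised men can have, and the section cannot be followed literally while also analysing all participants as allocated. The consequences are lost precision, an effect estimate for a narrower population than the one enrolled, and a choice about zeros left open until after the data are seen. Bias between the arms is not among them.

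The size is unknown. Under the assumptions shown (5% to 30% zeros, SD of about 2.67, 61 per arm, t approximation), power would fall from about 79% to between 77% and 64%. These figures illustrate the possible loss and do not estimate this trial's loss. Given the feasibility aim and the possibility that the unseen SAP already handles zeros, this is a should-fix: wrong as written, and simple to put right.

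**What to change.** In the primary model, replace log_e(x) with a covariate defined at zero. Either of these will do, provided that one is chosen before outcome data are seen:

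- log_e(x+1); or
- log_e(x) for x > 0, set to a fixed value (for example 0) at x = 0, together with an indicator for x = 0.

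Add one sentence saying that men with zero baseline episodes stay in the primary analysis, and make the SAP match, so that both statisticians implement the same rule. The change concerns the primary model only.

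The cost is a line of analysis wording, plus one extra parameter if the indicator is used. No further data or participants are needed.

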## Objectives

To establish the feasibility and optimal design of a full-scale RCT to test the effect on condom use and STI acquisition of the MenSS intervention website for men attending sexual health clinics:
Conduct a pilot trial to optimise the parameters for a phase III RCT of usual clinical care plus the IDI compared to usual clinical care only, using the primary outcome of self-reported condom use at 3-month follow-up.Optimise the data collection and analysis procedures for a health economic analysis for a future Phase III RCT.

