### Setting

Participants will be recruited from three sexual health clinics: The Homerton Hospital Department of Sexual Health, St Bartholomew's Sexual Health Centre, and City of Coventry Health Centre Integrated Sexual Health Services Department. These clinics serve a diverse range of patients in terms of age, socioeconomic status and ethnicity.

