### Randomisation

Once participants have been checked for eligibility, given informed consent, and submitted baseline data, they will be allocated by the computer algorithm randomisation system to either the intervention or control group. The participant will be informed with an automated message on the tablet computer, and this allocation will be unalterable.

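### The primary model's stated covariates leave out clinic in a three-clinic trial; this costs a little precision and causes no bias

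*Protocol article*

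**What the plan says.** Under Analysis of outcomes, the protocol article specifies the primary model in three sentences:

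- Model: "Analysis for the primary outcome will use a generalised mixed model, with log link and Poisson/mixed error".
- Covariates: the log of the baseline "number of episodes of unprotected vaginal sex and the experimental condition".
- Random effect: "The analysis will include a generalised (random effects) over-dispersion parameter". This is described as handling over-dispersion, not clinic.

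The same section adjusts the other sexual health comparisons for the baseline value of the outcome. Outcomes measured only at follow-up are compared between the groups with no covariate named.

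The Setting section states: "Participants will be recruited from three sexual health clinics". Under Randomisation, once baseline data are in, "they will be allocated by the computer algorithm randomisation system to either the intervention or control group". Neither that section, nor those on online procedures, allocation concealment and protection against bias, names clinic as a stratification factor. Clinic appears nowhere in the article as a covariate or random effect. A separate Statistical Analysis Plan is announced but is not shown.

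**The concern.** Clinic is a baseline characteristic available for every participant. Recruitment is on a tablet in the clinic waiting room, and at 12 months the notes are searched at the clinic where each man was recruited. Adjusting for site is routine in a multi-site trial because outcome levels often differ between sites for reasons that one baseline measure does not fully capture.

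If the three clinics differ in follow-up levels of unprotected sex, a model without clinic treats that difference as unexplained variation. With no stratification described, the arms may also differ by chance in their clinic mix, and that adds to the sampling error of the treatment estimate. What is at stake is precision: a somewhat wider interval and slightly lower power. The pilot is also meant to supply effect sizes for the power calculation of a phase III trial, so avoidable residual variation could carry over into that calculation.

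**Working it through.** **Inputs from the article (Setting; Sample size and power calculations).** Three clinics; 1:1 allocation; 166 men (83 per arm) for 90% power, or 122 (61 per arm) for 80% power, to detect a reduction of 1.35 episodes at two-sided α = 0.05. No SD and no clinic effect are given.

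**Step 1: the plan's own figures.** The SD is not stated, so it is back-solved from SD = 1.35 / [(z₀.₉₇₅ + z_power) × √(2/n)]:

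- n = 83, 90% power: 1.35 / [(1.960 + 1.282) × √(2/83)] = 2.683
- n = 61, 80% power: 1.35 / [(1.960 + 0.842) × √(2/61)] = 2.661

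The two agree closely, so the stated sizes are consistent with each other.

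**Step 2: power if clinic explained a share r of the residual variance.** The SD becomes 2.683 × √(1 − r); r is an assumption.

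| r | Power, 83 per arm | Power, 61 per arm |
|---|---|---|
| 0 | 90.0% | 79.4% |
| 1% | 90.3% | 79.8% |
| 2% | 90.6% | 80.2% |
| 5% | 91.4% | 81.4% |
| 10% | 92.7% | 83.4% |

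At 61 per arm the gain runs from 0 to 83.4 − 79.4 = 4.0 points.

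**Step 3: simulation of an over-dispersed count model.** Assumptions: 122 men, 61 per arm; clinics holding 40%, 30% and 30% of them; mean 4 episodes; rate ratio 0.6 (log −0.511) or 1; a prognostic baseline covariate in both fits; clinic effects of −s, 0 and +s on the log-rate scale; 1,500 runs per scenario.

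| s | Mean log rate ratio, without / with clinic | Power, without / with | Type I error, without / with |
|---|---|---|---|
| 0 | −0.518 / −0.518 | 68.6% / 67.7% | 6.1% / 6.4% |
| 0.2 | −0.506 / −0.506 | 65.7% / 66.8% | 7.0% / 7.4% |
| 0.4 | −0.522 / −0.520 | 63.3% / 68.3% | 6.5% / 7.7% |

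*Bias.* The estimates with and without clinic agree to within 0.002.

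*Type I error.* Both fits run a little above 5%, which reflects the simple over-dispersion correction used in the simulation. Leaving clinic out does not raise the error; it is slightly lower without clinic.

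*Power.* The Monte Carlo standard error of one power figure is about √(0.66 × 0.34 / 1500) = 1.2 points, so the differences at s = 0 and s = 0.2 amount to little or nothing. The 5-point difference at s = 0.4 is an upper figure, because the adjusted test is also slightly more liberal there. Using instead the empirical SDs of the estimates (0.239 without clinic, 0.229 with), the approximate powers are Φ(0.511/0.239 − 1.96) = Φ(0.18) ≈ 57% and Φ(0.511/0.229 − 1.96) = Φ(0.27) ≈ 61%, a gain of about 4 points.

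A second simulation, also with 122 men and the baseline count in the model, agreed: powers of 64.1% and 64.3% for the two fits when clinics do not differ, and gains of about 0.5 points at ±0.2 and 5 points at ±0.4.

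**The case against.** The strongest reply is that nothing here is wrong. With individual randomisation and no stratification described, a model without clinic is valid, and it already adjusts for the baseline value of the outcome, usually the strongest predictor. That stands, and it limits the point to precision.

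A second reply is that a journal article condenses the plan, that it does not say these are the only covariates, and that a Statistical Analysis Plan is promised. This stands in part: that plan may add clinic. But the article is not silent. It states what the explanatory variables will be, so an analysis plan that follows it leaves clinic out, and one that adds clinic departs from the published text.

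A third reply is that clinic indicators may be unworkable for rare outcomes in a pilot of 166. This stands for STI diagnoses and limits the fix.

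A reader might also infer more than the document supports:

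- **That the comparator differs by clinic.** The design is "usual clinical care plus the IDI compared to usual clinical care only". Variation in that care between sites is not described, and both arms receive it.
- **That the clinics are known to differ.** The Setting section says "These clinics serve a diverse range of patients in terms of age, socioeconomic status and ethnicity". This describes the breadth of patients served, not differences of one clinic from another.
- **That follow-up completion varies by clinic.** The primary outcome is collected online, with the same reminders and vouchers for all participants.

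**Conclusion.** The point holds as a minor, optional improvement. The article states a primary model without clinic in a three-clinic trial. Under assumed clinic log-rate spreads of 0 to ±0.4, this costs roughly 0 to 5 power points, with nothing lost if the clinics do not differ beyond the baseline count. The size rests wholly on assumed clinic effects.

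It would be wrong to go further and say that the omission biases the treatment effect. One can show, for example, that with one clinic's mean set at 1.25, 1.5 or 2.0 times the others, chance imbalance shifts the ratio of raw arm means by about 4%, 7% or 13% at the 95th percentile. Those figures ignore the baseline covariate that the plan does include, they are extremes rather than expected shifts, and they describe ordinary sampling error. In a pilot whose stated primary aim is recruitment, retention, engagement and acceptability, no decision described in the article turns on this.

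**What to change.** Add clinic to the explanatory variables of the primary model as a fixed effect with two indicator variables, and carry the same wording into the Statistical Analysis Plan before outcome data are examined; or state why clinic is left out. A fixed effect is preferable to a random one because three clinics are too few to estimate a between-clinic variance well.

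In the other outcome models, include clinic only where event counts support it. STI diagnoses may be too sparse, and the plan should then say that clinic is omitted for that reason. If the allocation algorithm does in fact stratify by clinic, the case for including clinic is stronger, and the stratification should be stated.

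The cost is one phrase and two degrees of freedom, with no new data. The downside is that nothing is gained if the clinics do not differ beyond what the baseline count already captures.
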